### Statistical analysis

Analyses will be carried out by intention to treat and will use multilevel logistic regression modelling with different distributions of errors according to the objective analysed for a factorial study controlled for the baseline antibiotic prescribing rate and with allowance for clustering by GP and health centre. The effects of various potential confounders related to clinical severity will be explored because of the potential for selection bias in an open trial. If interactions between interventions are not significant, the results will be presented as the main effects of each intervention (e.g., factorial groups with estimates controlling mutually for each intervention). The analysis will be performed using Stata 15 econometric software (StataCorp, College Station, TX, USA).

To study uncertainty, univariate and multivariate deterministic sensitivity analyses of the relevant parameters considered will be undertaken.

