**Methods/design:**

A cluster randomised, factorial, controlled trial aimed at including 20 primary care centres (*N* = 2940 patients) with patients older than 18 years of age presenting for a first consultation with an ALRTI will be included in the study. Primary care centres will be identified on the basis of socioeconomic data and antibiotic consumption. Centres will be randomly assigned according to hierarchical clustering to any of four trial arms: usual care, CRP testing, enhanced communication skills backed up with patient leaflets, or combined interventions. A cost-effectiveness and cost-utility analysis will be performed from the societal and national healthcare system perspectives, and the time horizon of the analysis will be 1 year. Two qualitative studies (pre- and post-clinical trial) aimed to identify the expectations and concerns of patients with ALRTIs and the barriers and facilitators of each intervention arm will be run. Family doctors and nurses assigned to the interventions will participate in a 2-h training workshop before the inception of the trial and will receive a monthly intervention-tailored training module during the year of the trial period. Primary outcomes will be antibiotic use within the first 6 weeks, duration of moderate to severe cough, and the quality-adjusted life-years. Secondary outcomes will be duration of illness and severity of cough measured using a symptom diary, healthcare re-consultations, hospital admissions, and complications. Healthcare costs will be considered and expressed in 2021 euros (year foreseen to finalise the study) of the current year of the analysis. Univariate and multivariate sensitivity analyses will be carried out.

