### Sample size calculation

To calculate the sample size, we will use a type I error of 5% and a power of 80%, and we will assume that antibiotic prescribing will decrease by at least 15%, from 60% to 45%, in any one of the three intervention groups. We will also assume a drop-out rate of 12% and an intra-cluster correlation coefficient for antibiotic prescribing within practices of up to 0.07, based on two recent studies [14, 16]. We estimate that a sample of 788 (197 × 4) patients will be needed. Allowance for an inflation factor of 3.73 due to clustering and rounding of numbers for the four subgroups give an overall sample size of 2940 [17]. As a consequence, at least 147 patients will be recruited per centre.

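### With only 20 randomised centres, the named multilevel logistic model needs a stated small-sample method: ordinary Wald testing would give about 8–13% type I error for antibiotic use, not 5%

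*Protocol article*

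**What the plan says.** The design is described in the Abstract of the Protocol article as "A cluster randomised, factorial, controlled trial aimed at including 20 primary care centres". Under Trial interventions, whole centres are randomised to four arms: usual care, CRP testing, communication skills, or both.

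The Statistical analysis section says the analyses "will use multilevel logistic regression modelling with different distributions of errors according to the objective analysed". The model is factorial, adjusts for baseline prescribing rate and allows for clustering at GP and centre level. Stata 15 is the software. If the interaction is not significant, results are given as main effects. The section names no estimation method, test statistic, reference distribution or degrees-of-freedom rule. It neither adopts nor rules out a small-sample correction.

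The Sample size calculation section gives the intended error rate: "we will use a type I error of 5% and a power of 80" per cent.

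**The concern.** Each intervention is constant within a centre, so the evidence on it comes from differences between centres. There are 20 of these, however many patients each one recruits. A multilevel logistic model fitted by maximum likelihood and tested against the normal distribution goes wrong in two ways with so few clusters. It underestimates the between-centre variance, because it makes no allowance for the centre-level parameters it has estimated. It also uses 1.96 where a larger t value is needed.

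If the analysis is run that way, P values and confidence intervals for antibiotic use will be too optimistic. The interaction test is affected too. It decides whether the trial is reported as main effects, so its distortion feeds into the form of the result as well as its precision.

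**Working it through.** **Inputs from the Protocol article.** Prescribing "from 60% to 45%, in any one of the three intervention groups"; "a drop-out rate of 12" per cent; "intra-cluster correlation coefficient for antibiotic prescribing within practices of up to 0.07"; 20 centres; 147 patients recruited per centre.

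**Step 1: the plan's own figures.** The pooled two-proportion formula, two-sided 5%, 80% power (sidedness is not stated, but two-sided reproduces the figure), with mean proportion 0.525:

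n = [1.96·√(2·0.525·0.475) + 0.8416·√(0.60·0.40 + 0.45·0.55)]² / 0.15² = 172.8, so 173 per arm.

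173/0.88 = 196.6, so 197 per arm, which agrees with "We estimate that a sample of 788 (197 × 4) patients will be needed". Then 788 × 3.73 = 2939, rounded to 2940, and 2940/20 = 147 per centre. After drop-out, 147 × 0.88 = about 129 are analysed per centre. (The factor 3.73 equals 1 + 39 × 0.07, which implies clusters of 40 rather than 147. That is a separate point and is not used below.)

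**Step 2: how much information is between centres.** The between-centre share of the variance of a centre mean is 0.07/(0.07 + 0.93/129) = 0.91. Precision is therefore governed by the number of centres.

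**Step 3: analytic approximation.** Let df = 20 minus the number of centre-level parameters. Using 1.96 in place of a t value gives P(|t| > 1.96) = 6.8% at 16 df and 6.9% at 15 df. Maximum likelihood also divides the between-centre sum of squares by 20 instead of by df, so the true rejection rate is about P(|t_df| > 1.96·√(df/20)). At 16 df this is P(|t| > 1.753) = 9.9%.

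**Step 4: simulation under the null.** 20 centres, 5 per arm, 129 patients each, 60% prescribing; random-intercept logistic model fitted by maximum likelihood with adaptive quadrature; Wald z-test at 1.96. There were 2000 data sets at each of three random-intercept variances (Monte Carlo standard error about 0.6 points):
- 0.248, which is ICC 0.07 on the latent scale: 0.07 × 3.29/0.93;
- 0.292, which is ICC 0.07 on the proportion scale: 0.07/0.24;
- 0.10, a lower value for sensitivity.

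Results from separate runs are in brackets.

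| Contrast | df | Step 3 | Simulated type I error |
|---|---|---|---|
| Main effect, no covariate | 17 | 8.8% | 7.8–9.3% (8.5%, 8.6%) |
| Main effect, baseline covariate | 16 | 9.9% | 9.2–10.0% (10.5%) |
| Arm vs usual care, no covariate | 16 | 9.9% | (9.4%, 9.7%) |
| Arm vs usual care, baseline covariate | 15 | 11.0% | 12.0–13.0% (11.5%) |
| Interaction, baseline covariate | 15 | 11.0% | 10.3–11.7% |
| Main effect, centre-level t-test with covariate | 16 | 5% by design | 4.7–5.1% |

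The 9.4% is 330 rejections in 3500 data sets, so nominal 95% intervals for that contrast cover about 90%. The last row shows that a centre-level t-test on the same data restores the nominal level.

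**The case against.** The strongest reply is that this is built on silence. The article names a class of model, not a Wald z-test, and that model is compatible with a t reference and a restricted-likelihood variance. It is a condensed article, the analysis plan is not shown, and degrees of freedom are commonly settled there. The 5% is an input to a sample size formula, and naming a model elsewhere does not contradict it.

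Much of that stands. A reader might infer that the plan commits the trial to a true error rate of 9–10%. The article does not support this, because it never says that no correction will be used. Three further limits also stand:
- Five centres per arm is only 20/4 and is not stated. The default presentation is main effects, which compare 10 centres with 10.
- No single figure covers every contrast.
- A reader might carry the figures over to cough duration and QALYs. The ICC of 0.07 is given for antibiotic prescribing only, no ICC is given for those two outcomes, and neither was simulated.

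What does not stand is that the matter is merely missing detail. The article fixes the model, the number of randomised units and an interaction rule that depends on significance. Run in the ordinary way, that combination gives anti-conservative tests, and nothing in the section guards against this.

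**Conclusion.** The point holds in conditional form. If the multilevel logistic model is tested with ordinary maximum-likelihood Wald z inference, type I error for antibiotic use is about 8–13% across contrasts, and about 9–10% for the covariate-adjusted main effects that are the default report. The interaction test runs at about 10–12%. The critical value alone accounts for only about 7%; the rest comes from underestimated between-centre variance.

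The figures assume equal centre sizes, normal centre effects, equal allocation, an ICC of about 0.07 (with the lower variance as sensitivity), and a baseline covariate that acts at centre level and has no effect. The GP level named in the plan was not simulated, and the direction of its influence was not examined. For cough duration and QALYs the mechanism is the same, because the interventions are still allocated by centre, but the size is unknown.

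**What to change.** Add to the Statistical analysis section, or confirm in the analysis plan, that tests and confidence intervals for the intervention contrasts and for the interaction use a small-sample method. Either of these would do:
- a t reference with between-centre degrees of freedom (20 minus the number of centre-level parameters) and REML-type variance;
- a centre-level analysis of covariate-adjusted residuals.

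As a check, add a permutation test that re-allocates centres as the actual randomisation did, including any stratification or grouping of centres. Apply the rule to all three primary outcomes, each with its own error distribution.

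The cost is wording, a little programming and wider intervals. Under the Step 3 approximation at 16 df (t value 2.12), the widening relative to uncorrected intervals is (2.12/1.96) × √(20/16) = 1.21, or about a fifth. That width is what 20 centres can honestly support. No extra patients or data are needed.

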### Setting and timing

General practices throughout Catalonia in the localities of the study centres (with different socioeconomic levels) will be approached, and at least three pairs of clinicians (GPs and nurses) in eligible centres will be invited to participate. Eligible centres will be stratified depending on the socioeconomic level and baseline antibiotic consumption, and only those that had not previously used any intervention to reduce antibiotic prescribing rates will be selected. They are expected to include 150 patients (75 patients in each autumn-winter season) in the trial.

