### Outcome measures

During the index consultation GPs will document the duration of the illness, the severity of cough and other symptoms (rated 0, not problematic; to 6, severely problematic), and the severity of the infections. After randomisation a more detailed case report form (CRF) will be used in the follow-up consultations and will include the same details as the index form plus medical history, current medications, smoking status, findings of structured examination, whether CRP is tested, and whether the booklet is used. The primary outcome measures will be antibiotic consumption within the first 6 weeks, as documented in the CRFs and double-checked by the Pharmacy Unit of the Catalan Institute of Health, which can track if the antibiotic has been dispensed at any of the Catalan pharmacies; the duration of moderate to severe cough (i.e., those rating their cough as 3 or more by means of a Likert scale); and the quality-adjusted life-years (QALYs), which will be collected by means of the EQ-5D-5L questionnaire within the first 6 weeks (Table 1).

**Table 1 Tab1:** Schedule of enrolment, interventions and assessments for the clinical trial

Time point	Study period November 4, 2019–April 30, 2021		
	Day 1	Week 2	Week 6
Enrolment			
Medical history and physical examination	X		
Explanation of the study and informed consent	X		
Initial CRF	X		
Giving out of the symptom diary, up to week 2	X		
Interventions			
CRP rapid test if needed (only among those patients visited by professionals assigned to the CRP intervention groups)*	X		
Use of an interactive booklet (only among those patients visited by professionals assigned to the enhanced communication skill intervention groups)*	X		
Assessments			
Assessment of the clinical outcome		X	X
Collection and review of the symptom diary		X	
EQ-5D-5L questionnaire	X	X	X
Antibiotic consumption	X	X	X
Use of drugs other than antibiotics	X	X	X
Tests ordered by clinicians	X	X	X
Patient satisfaction with care		X	X
Patient perception of the usefulness of the information received		X	X
Patient future consulting intentions		X	X
Absenteeism	X	X	X
Evaluation of adverse events		X	X
Number of re-consultations to primary and secondary care and number of complications regarding the ALRTI			X

*Abbreviations: ALRTI* acute lower respiratory tract infection, *CRF* case report form, *CRP* C-reactive protein, *GP* general practitioner

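### The QALY model names no adjustment for Day 1 utility, and only one of the two factors used to stratify centres is carried into the analysis

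*Protocol article*

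**What the plan says.** Under Statistical analysis, the protocol article describes a multilevel model whose error distribution changes with the objective. It is "controlled for the baseline antibiotic prescribing rate and with allowance for clustering by GP and health centre". A prescribing rate belongs to a clinician or a centre, so the only named covariate is not measured on the patient. The same section adds: "The effects of various potential confounders related to clinical severity will be explored because of the potential for selection bias in an open trial". It does not say which severity variables, or whether they enter the primary model.

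The other relevant statements are:

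- **Outcomes.** Outcome measures lists three primary outcomes: antibiotic use, duration of moderate to severe cough, and QALYs from EQ-5D-5L over six weeks. Table 1 schedules EQ-5D-5L on Day 1, at Week 2 and at Week 6.
- **Centres.** Setting and timing says: "Eligible centres will be stratified depending on the socioeconomic level and baseline antibiotic consumption". The abstract says: "Centres will be randomly assigned according to hierarchical clustering to any of four trial arms". Trial interventions describes randomisation only as computer-generated random numbers.
- **Order of events.** The notes to Table 1 put randomisation on 21 October 2019 and the workshops at the end of that month. Trial status says recruitment opened on 18 November 2019. Trial interventions states that neither GPs nor patients can be masked.

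**The concern.** The covariate that is fixed suits antibiotic use. It is not a baseline for a utility outcome. A QALY built from three EQ-5D-5L measurements contains the Day 1 value, so any difference between arms at Day 1 enters the outcome arithmetically, before any intervention effect.

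Randomising centres does not protect against this when patients are recruited afterwards by clinicians who know their arm. Eligibility also depends on the clinician's belief that the cough is an infectious ALRTI, so the mix of patients may shift by arm. The plan itself recognises selection bias as a risk. At stake is the contrast in a primary outcome that is also the denominator of the incremental cost-utility ratio.

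The second part is smaller. Of the two factors used to stratify centres, the model carries a close counterpart of one (baseline prescribing) and not the other (socioeconomic level). Between-centre variation limits precision with 20 centres, and a centre-level predictor already in hand may reduce it.

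**Working it through.** **The plan's own figure.** The document gives no figure for covariate adjustment. Its sample size does not depend on one: 173 per group for 60% against 45% (two-sided 5%, 80% power), 173/0.88 = 197, 197 × 4 = 788, and 788 × 3.73 = 2939, stated as 2940. This point leaves those numbers unchanged. Whether 3.73 is the right inflation is a separate question and is not used here.

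**Weight of Day 1 in the QALY.** Assumption: the usual trapezoid area under the curve, with measurements at 0, 14 and 42 days. The article does not state the QALY formula.

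QALY = [14 × (u0 + u2)/2 + 28 × (u2 + u6)/2] / 365 = (7·u0 + 21·u2 + 14·u6) / 365

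The Day 1 weight is 7/365 = 0.0192 QALY per unit of utility. An imbalance d at Day 1 therefore contributes, through that term alone:

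| Assumed d | QALY contributed |
|---|---|
| 0.01 | 0.00019 |
| 0.02 | 0.00038 |
| 0.05 | 0.00096 |

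For scale, suppose the intervention truly changes utility by e at both Week 2 and Week 6. It then contributes (21 + 14)·e/365 = 35e/365, and the Day 1 term amounts to 7d/35e = 0.2 × d/e of it. That is 10% for d = 0.01 and e = 0.02, 20% when d = e, and 50% for d = 0.05 and e = 0.02. All values of d and e are assumed. If part of the imbalance persists to later visits, the contribution exceeds the Day 1 term.

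**Socioeconomic level.** Inputs from Sample size calculation: 147 patients per centre, 12% drop-out, ICC up to 0.07. This gives 147 × 0.88 = 129.4 analysed per centre. The between-centre share of the variance of a centre mean is 0.07 / (0.07 + 0.93/129.4) = 0.907.

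If socioeconomic level explains a share R² of the between-centre variance, the SE of a centre-level contrast is multiplied by √(1 − 0.907·R²). The baseline prescribing rate is already in the model, so only what socioeconomic level explains beyond it counts. The second row therefore assumes that this adjustment has cut the ICC to 0.03, giving a share of 0.03 / (0.03 + 0.97/129.4) = 0.80.

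| ICC | R² = 0 | R² = 0.1 | R² = 0.3 | R² = 0.4 |
|---|---|---|---|---|
| 0.07 | 1.00 | 0.95 | 0.85 | 0.80 |
| 0.03 (assumed) | 1.00 | 0.96 | 0.87 | 0.82 |

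Every R² is assumed. The ICC is for antibiotic prescribing; none is given for QALYs or cough.

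**Price in degrees of freedom.** 20 centres less four arm means less the prescribing rate leaves 15. One further term leaves 14, so the critical t goes from 2.131 to 2.145, 0.7% wider. Two terms leave 13, with t = 2.160, 1.4% wider.

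**The case against.** The strongest reply is that a journal article condenses the analysis, and covariate lists commonly sit in a statistical analysis plan that is not shown. That would answer a complaint about silence. Here the article states a model and names its covariate for all objectives, so the choice can be judged as written. A fuller plan may already contain the correction, and if so the two texts need only be aligned.

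Other parts of the reply stand and limit the point:

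- **Severity.** A reader might infer that clinical severity is ignored. It is not: the plan says it will be explored, and for the right reason. Unmasked, trained clinicians rate cough and infection severity at the index visit, so those ratings may themselves be affected by arm. Keeping them out of the primary model is defensible. The gap is that neither the variables nor their role is fixed.
- **Bias from the socioeconomic factor.** A reader might infer that leaving it out biases the results. Omitting a factor used to stratify centres mainly leaves standard errors larger than necessary. The bias argument belongs to patient-level baselines.
- **Randomisation stratum.** A reader might take socioeconomic level to be one. The text says eligible centres are stratified on it and does not explain the hierarchical clustering, so its role in allocation is unclear.
- **Magnitudes.** Any percentage for bias or lost precision rests on assumed inputs. If socioeconomic level and prescribing are strongly related across centres, the further gain could be close to nil. Factorial main effects also compare about 10 centres with 10, not 5 with 5.
- **Case report form.** Outcome measures says "After randomisation a more detailed case report form (CRF) will be used in the follow-up consultations" and places history, smoking and examination there, while Table 1 has history and examination on Day 1. The wording needs reconciling, but nothing in the plan proposes adjusting for values recorded at follow-up.

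**Conclusion.** The point holds in two parts of unequal weight.

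The main part is the QALY outcome. As written, its model adjusts for a prescribing rate and not for Day 1 utility. Under the usual area-under-the-curve calculation, any Day 1 imbalance enters the contrast at about 0.019 QALY per unit of utility from that term alone. An imbalance is plausible because recruitment is open and follows centre randomisation, but its size and direction cannot be derived from the documents.

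The lesser part is precision. Leaving out socioeconomic level may widen standard errors. Under the assumed R² values the possible SE reduction runs from none to about 20%, against a loss of roughly 1% in the critical value. This is a worthwhile, inexpensive improvement to the analysis text. It does not show that the trial's conclusions would be wrong, and it does not affect the sample size.

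**What to change.** Amend Statistical analysis as follows:

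1. In the QALY model, prespecify Day 1 EQ-5D-5L utility as a covariate. State that the questionnaire is completed before the consultation can influence the answers, if that is the case.
2. In all models, include the centre's socioeconomic level, in the form used in selecting or allocating centres, alongside the baseline prescribing rate. Say what role it played in allocation.
3. Replace the open exploration of severity confounders with a named set of clinician-rated Day 1 severity variables, used in a prespecified supporting analysis. Use Day 1 values only.

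As a separate clarification, reconcile the case report form description in Outcome measures with Table 1.

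The cost is a few sentences. The EQ-5D-5L and index-visit severity data are already scheduled, and centre socioeconomic data are already used to identify centres. The statistical price is one or two between-centre degrees of freedom out of about 15, more if socioeconomic level is entered with many categories, so a single term or few levels is preferable.

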### Resource use and costs

Micro-costing techniques will be used to estimate the healthcare costs for patients with acute cough in the different interventions. The costs will be presented in 2021 euros (year foreseen to finalize the study). Primary data of the ISAAC-CAT clinical trial will be used whenever possible. The costs will include the costs of treatment to control the acute cough and management of these patients. The cost of treatment will depend on the state of health of the patient but may include the costs of the different therapies prescribed, including those recommended to be purchased at the pharmacies. The costs of management will include the cost of primary care and secondary care visits within the first 6 weeks as well as any diagnostic tests performed and the number of days of patient absenteeism. The cost of the interventions will cover the continuous training, including the workshop and the monthly delivery of training microcapsules, the cost of the booklets, the cost of the CRP machine, and the reagents used.

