### Cost-effectiveness and cost-utility analyses

The cost-effectiveness analysis will be conducted comparing costs and effectiveness/utility, measured in natural units and QALYs, respectively, of the different alternatives to usual practice. In most cases the data will be obtained from the ISAAC-CAT clinical study. The comparison will be performed using the incremental cost-effectiveness ratio and the incremental cost-utility ratio, defined as the ratio of the difference in costs and the difference in effectiveness or utility. The results will be expressed in terms of euros per unit of effectiveness.

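### The one method named for economic uncertainty is deterministic, so incremental cost, the ICER and the ICUR have no stated sampling or clustering uncertainty

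*Protocol article*

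**What the plan says.** All places are in the Protocol article.

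- **Uncertainty.** The last sentence of Statistical analysis reads "To study uncertainty, univariate and multivariate deterministic sensitivity analyses of the relevant parameters considered will be undertaken". The Abstract (Methods/design) has, directly after its sentence on healthcare costs, "Univariate and multivariate sensitivity analyses will be carried out". That placement is why the sentence is read here as concerning the economic evaluation.
- **Source of the data.** Resource use and costs: "Primary data of the ISAAC-CAT clinical trial will be used whenever possible". Cost-effectiveness and cost-utility analyses: "In most cases the data will be obtained from the ISAAC-CAT clinical study".
- **What is reported.** Cost-effectiveness and cost-utility analyses: "The comparison will be performed using the incremental cost-effectiveness ratio and the incremental cost-utility ratio".
- **General model.** Statistical analysis opens with "multilevel logistic regression modelling with different distributions of errors according to the objective analysed" and, later in the same sentence, "with allowance for clustering by GP and health centre".
- **Outcomes.** Abstract: "Primary outcomes will be antibiotic use within the first 6 weeks, duration of moderate to severe cough, and the quality-adjusted life-years". Costs are in neither the primary outcomes nor the table of secondary outcomes (Table 2), although some cost components, such as re-consultations and sick leave, are.

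**The concern.** This is mainly an economic evaluation alongside a trial, not a model fed by literature values. Its costs and QALYs are sampled from patients who are grouped in a small number of randomised centres. Deterministic sensitivity analysis asks how the answer moves when an input is set to another value. That suits a unit price, which has no sample behind it. It does not say how far the observed differences in cost and QALYs could have arisen by chance, how the two vary together, or how much of each is a difference between centres.

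The reported quantities are ratios, and a ratio is unstable when its denominator is small. The EQ-5D-5L is collected to week 6 (Outcome measures, Table 1). If QALYs are counted over that window only, a patient in full health throughout accrues at most 6/52 = 0.115 QALY, so differences between arms will be a fraction of that. A point ICUR with deterministic ranges around it could then present a chance difference between a few centres as an efficient strategy. Efficiency is part of the stated aim of the trial (Objectives).

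**Working it through.** **1. The cluster structure, from the plan's own figures** (Sample size calculation). Inputs: 60% against 45%, type I error 5% (taken as two-sided), power 80%, drop-out 12%, inflation factor 3.73, total 2940; 20 centres (Abstract).

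- Two proportions, pooled variance under the null, no continuity correction: n = [1.96√(2 × 0.525 × 0.475) + 0.842√(0.60 × 0.40 + 0.45 × 0.55)]² / 0.15² = 172.8, so 173 per arm.
- Drop-out: 173 / 0.88 = 196.6, so 197 per arm; 197 × 4 = 788, as stated.
- Clustering: 788 × 3.73 = 2939.2, rounded to 2940; 2940 / 20 = 147 per centre, as stated.

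The stated figures reproduce. They are used here only for the number per centre; whether 3.73 is the right inflation factor is a separate question. Evaluable per centre: 147 × 0.88 = 129.4, taken as 129. Equal allocation would give 20 / 4 = 5 centres per arm, which the article does not state.

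**2. What each stated method can deliver.**

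| Quantity | Multilevel model by objective | Deterministic analysis |
|---|---|---|
| QALY difference | Plausibly covered, with clustering, as a primary outcome | No sampling uncertainty |
| Incremental cost | Unclear: not a listed outcome, and the clause is worded as logistic regression | No sampling uncertainty |
| ICER, ICUR | Not covered: a ratio of two differences, not a modelled outcome | No sampling uncertainty |

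Separate models for cost and effect would not close the last row. For a threshold λ, net monetary benefit is λΔE − ΔC, and its variance is λ²Var(ΔE) + Var(ΔC) − 2λCov(ΔE, ΔC). The covariance is not available from two separate fits.

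**3. Size of clustering, as an illustration.** The article gives an intra-cluster correlation for antibiotic prescribing (up to 0.07) and none for cost or QALY. The range 0.005 to 0.05 is an assumption. With design effect DE = 1 + (129 − 1) × ICC, the standard error is multiplied by √DE, and (DE − 1)/DE is the share of the variance added by clustering:

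| Assumed ICC | DE | √DE | (DE − 1)/DE |
|---|---|---|---|
| 0.005 | 1.64 | 1.28 | 39% |
| 0.01 | 2.28 | 1.51 | 56% |
| 0.02 | 3.56 | 1.89 | 72% |
| 0.05 | 7.40 | 2.72 | 86% |

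Ignoring clustering would understate standard errors by a factor of about 1.3 to 2.7. Clustering contributes more than half of the variance only when 128 × ICC exceeds 1, that is, above an ICC of about 0.008.

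**4. Few centres.** With 5 centres against 5, there are 8 degrees of freedom at centre level and the 97.5% t quantile is 2.306 instead of 1.96, so an interval is a further 18% wider (2.306 / 1.96 = 1.18).

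**The case against.** The strongest reply is that Statistical analysis already commits to multilevel modelling chosen by objective, with clustering by GP and centre. QALYs are a primary outcome, so their difference between arms would naturally be estimated under that clause. A reader might infer from the deterministic sentence that cost and QALY results alike carry no sampling or clustering uncertainty. For QALYs the text does not support that, and this part of the objection stands.

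Second, a reader might infer that deterministic analysis is the only method that will be used. The article does not say so. It says what will be done and names nothing else, and a fuller analysis plan, not at hand, could add a method. That limits the claim to what is named. It does not remove the point: the article states a method for uncertainty, and that method cannot produce sampling uncertainty for the ratios it reports.

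Third, the factor of 1.3 to 2.7 compares a clustered standard error with a patient-level one that the plan nowhere proposes, and it rests on an assumed ICC. This also stands, so the factor shows what is at stake and does not measure an error in the plan. Nor is it certain that clustering dominates the variance: at an ICC of 0.005 it adds 39%.

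Fourth, if the interaction is not significant, results are presented as factorial main effects, which would be 10 centres against 10 under equal allocation. However, Objectives describes an economic evaluation of four strategies against current practice, which points to comparisons by arm.

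**Conclusion.** The point holds in a limited form. The sole method named for uncertainty in the economic evaluation is deterministic, while the inputs are mostly sampled from patients in 20 randomised centres. No stated method gives sampling uncertainty, centre clustering or cost-effect correlation for incremental cost, the ICER or the ICUR. The QALY difference on its own is plausibly covered by the multilevel clause.

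The size can only be illustrated: standard errors about 1.3 to 2.7 times larger than if clustering were ignored, for 129 evaluable patients per centre and an assumed ICC of 0.005 to 0.05. The effectiveness conclusions are not affected. The cost-effectiveness and cost-utility conclusions lack a stated inferential basis, and this should be put right before the economic analysis is run.

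**What to change.** In Statistical analysis, add to the sentence on uncertainty that incremental cost, incremental effect or QALY, and net monetary benefit will be estimated jointly, by a method that respects centre clustering and cost-effect correlation, and reported with 95% intervals and cost-effectiveness acceptability curves. Two options:

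- a bivariate multilevel model, or a multilevel model on net benefit, with a small-cluster correction;
- a two-stage bootstrap that resamples centres and then patients within arm, with its limits acknowledged. With 5 centres per arm, if allocation is equal, the first stage recovers on average only (5 − 1)/5 = 80% of the variance of the arm mean that the spread between centre means implies.

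State also whether the multilevel clause covers costs, and with which error distribution. Keep the deterministic analyses for inputs and scenarios that are not sampled: unit costs, device life, perspective, time horizon and values taken from outside the trial.

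No new data are needed. The price is some extra programming and economic results that will be stated with less certainty.
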